### Avoiding bias

The trial design includes double-masking to avoid bias in the assessment of outcomes. This minimizes co-interventions. Every effort is made to avoid unmasking of participants. In the event that unmasking cannot be avoided, sites notify the MiTy coordinating centre, and the designated programmer securely provides the Site Investigator with the participant’s allocation.

### Sample size and power calculation

The sample size was calculated using the incidence of the composite outcome from the validated Nova Scotia Atlee Perinatal Database^.^ In this database, the incidence of the composite outcome was 62 %. For the purpose of calculating the sample size, a conservative value of 50 % was assumed. A relative risk reduction of 25 % (i.e., from 50 to 37.5 %) was considered clinically relevant. A total of 246 women per treatment group gives 80 % power if the addition of metformin decreases the risk of the composite outcome by 25 % (2-tailed α of 0.05). Accounting for 2 % loss to follow-up, a sample size of 250 per treatment group or 500 in total is planned. If the incidence is as high as 62 %, we have over 90 % power for a relative risk reduction of 25 and 78 % power for a relative risk reduction of 20 %. Although our hypothesis is that the addition of metformin will decrease the event rate of the primary composite outcome, we cannot be sure that we are not causing harm, and therefore we are using a two-sided alpha for the sample size calculation.

### Data analysis

#### Interim analysis and safety considerations

There is one planned interim analysis of the composite outcome after 50 % of subjects (*n* = 246) have completed the Postpartum Visit (telephone interview). Using the O’Brien–Fleming procedure [33], the interim analysis will use a significance level of 0.003 for stopping the trial early. The MiTy coordinating centre will prepare the data for the interim analysis and the analysis will be sent to the statistician without unmasking the groups. After analysis the data will be sent to the Data Safety Monitoring Board (DSMB). The DSMB is made up of experts from endocrinology, obstetrics, epidemiology, and clinical trials methodology. The DSMB will convene by teleconference for the interim analysis. If the overall rate of adverse outcomes is larger than expected, or if there are unanticipated adverse events, the DSMB will have the right to analyze unmasked data.

The Steering Committee receives a summary of all reported serious adverse events (SAEs) at regular scheduled meetings (quarterly). The Steering Committee may be requested to review SAEs (masked) off-cycle as determined by the Working Group. The Working Group is made up of the principal investigator, some members of the Steering Committee, and members of the coordinating centre. If reported (masked) SAEs are of concern to members of the Steering Committee, or if there is an emerging pattern or unexpected frequency of events, the DSMB will be notified and information forwarded to them for review. Otherwise, all adverse events are reviewed by the DSMB at the time of the planned interim analysis.

#### Final Analysis

An “intention-to-treat” analysis will be performed, with subjects analyzed in the group to which they were randomized. The primary analysis will calculate the relative risk (and 95 % CI) of the composite neonatal outcome between the treated and control groups, stratifying by site and BMI group using a log-binomial regression model [34], and test the null hypothesis that the relative risk is equal to 1. We will estimate an overall absolute risk reduction and its 95 % CI and use this to compute a number needed to treat to benefit with metformin to avoid one adverse composite outcome. A similar analysis will be carried out for each of the dichotomous secondary outcomes. Continuous secondary outcomes measured at delivery will be compared using a two sample t-test or, if necessary, a bootstrap hypothesis test. The repeated measurements on HbA1c will be compared between groups using a linear mixed effects model. If important covariates remain imbalanced between treatment groups despite the stratified randomization, these covariates will be added to the log-binomial model and the difference between adjusted and unadjusted relative risks will be examined to assess the impact of this imbalance. All analyses will use a 2-tailed α of 0.05.

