## Methods/Design

### Overall study design

This is a multicentre, randomized, double-masked, placebo-controlled trial in women with type 2 diabetes in pregnancy. Participating sites comprise 21 centres in Canada and 1 centre in Australia. Women with type 2 diabetes in pregnancy, between 6^+0^ and 22^+6^ weeks gestation who are currently on insulin, are eligible. Eligible women are randomized to receive either metformin or placebo, to be added to their usual insulin regimen. Patients, caregivers and outcome assessors are blinded to which intervention is received. Baseline data are obtained at the time of randomization and at 4 week intervals until delivery. The primary outcome is a composite of perinatal outcomes. The analysis will be conducted using an intention-to-treat approach.

Primary Research Question: Among pregnant women with diagnosed type 2 diabetes mellitus, does the addition of metformin to a standard regimen of insulin, increase or decrease the incidence of adverse perinatal outcomes as defined by a composite of pregnancy loss, preterm birth, birth injury, respiratory distress, neonatal hypoglycemia and NICU admission longer than 24 h, compared with women treated with insulin plus placebo?

This trial is funded by the Canadian Institute of Health Research MOP 106678. The metformin and placebo tablets have been donated by Apotex Inc.

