### Recruitment

Women who meet eligibility criteria and who are being seen in obstetric or endocrine clinics are approached about participation in the trial and given information pamphlets describing the study. Those women who are interested are asked to sign a consent form. Women are told that participation is voluntary and that they can withdraw at any time without affecting their clinical care. At baseline a medical history is obtained along with other baseline demographics and concomitant medications including insulin regimen and dose (see Table 1). Weight, height and blood pressure are measured and recorded and blood samples are assessed locally for glycemic control, and renal parameters (serum creatinine and albumin to creatinine ratio).

**Table 1 Tab1:** Data Collection Schedule

	*At Entry*	*At Each Prenatal Visit*	*Every 4 Weeks*	*At End of Pregnancy*
Demographics:				
Age	x			
Parity	x			
Duration of Diabetes	x			
Diabetes Complications	x			x
Hypertension	x	x		x
Ethnicity	x			
HbA1c	x		x	x
Serum Creatinine	x			At 36 weeks GA
Hypoglycemic Episodes	x	x		x
Maternal weight, height	x	x		x
Maternal insulin dose	x	x		x
Insulin type used	x			
No. of Prenatal Visits				x
Delivery Information				x
Preeclampsia				x
Cord blood for c-peptide and cord gases				x
Infant Data				x
Neonatal skin folds				x

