### Randomization

Randomization occurs between 6^+0^ and 22^+6^ weeks gestation (see Fig. 1). Participants are assigned via the Centre for Maternal, Infant and Child Research trial website at Women’s College Hospital, to receive metformin or placebo in a 1:1 ratio, in randomly chosen block sizes. The trial randomization stratifies for site and body mass index (<30 or ≥30 kg/m^2^) calculated at the time of randomization.

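### Continuous secondary outcomes at delivery get an unadjusted t-test that omits the randomisation strata and the available entry values: valid, but conservative and imprecise

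*Protocol article*

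**What the plan says.** The Final Analysis section names the test for this group of outcomes: "Continuous secondary outcomes measured at delivery will be compared using a two sample t-test or, if necessary, a bootstrap hypothesis test". It mentions no stratum and no covariate.

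The rest of the article treats the strata differently:

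- Randomization: "The trial randomization stratifies for site and body mass index", with BMI split at 30 kg/m². Overall study design: "Participating sites comprise 21 centres in Canada and 1 centre in Australia". That is 22 sites, so up to 22 × 2 = 44 strata.
- The primary outcome is analysed "stratifying by site and BMI group using a log-binomial regression model". For the binary secondary outcomes, "A similar analysis will be carried out for each of the dichotomous secondary outcomes".
- The provision for imbalanced covariates reads "these covariates will be added to the log-binomial model and the difference between adjusted and unadjusted relative risks will be examined". It is confined to that model and does not reach the continuous outcomes.
- One continuous outcome is handled separately: "The repeated measurements on HbA1c will be compared between groups using a linear mixed effects model".

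Table 1 schedules maternal weight and the item "Maternal insulin dose" at entry, at each prenatal visit and at the end of pregnancy. Weight gain and insulin doses are both listed under Secondary outcomes.

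**The concern.** When allocation is balanced within strata that predict the outcome, the difference in means varies less than an ordinary two-sample t-test assumes. The t-test leaves the between-stratum variation in its standard error, so that standard error is too large. The test then rejects less often than its nominal 5%, and its interval is wider than it need be.

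An entry value that predicts the final value also removes noise when it enters as a covariate, and the trial already collects such values for weight and insulin dose. Both outcomes are central to the rationale, which expects metformin to lower insulin doses and weight gain. At stake is how precisely these effects are estimated, and whether the continuous and binary secondary outcomes are analysed on the same footing.

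**Working it through.** **The plan's own figure.** The only power statement concerns the binary composite: 50% against 37.5%, 246 per group, 80% power, two-sided 0.05. The pooled two-proportion formula gives 247 per group, and 246 per group gives 79.99% power, so the figure reproduces. It does not depend on the present point. The article gives no variance, effect size or power for any continuous outcome, so R² (the share of variance explained by the strata), ρ (the correlation of entry with final value) and the standardised difference of 0.25 are assumptions.

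**Step 1: omitting the strata.** With n per group and balance within strata, the true variance of the difference is (2/n)σ²(1 − R²), while the t-test estimates (2/n)σ². Hence:

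- true alpha = 2[1 − Φ(1.96/√(1 − R²))]
- interval width relative to the correct one = 1/√(1 − R²)
- with n = 246, √(2/246) = 0.0902 and 0.25/0.0902 = 2.77, so power is Φ((2.77 − 1.96)/√(1 − R²)) for the t-test and Φ(2.77/√(1 − R²) − 1.96) for the adjusted model

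| R² | 1.96/√(1 − R²) | True alpha | Width ratio | Power, t-test | Power, adjusted |
|---|---|---|---|---|---|
| 0 | 1.960 | 0.050 | 1.000 | 79% | 79% |
| 0.05 | 2.011 | 0.044 | 1.026 | 80% | 81% |
| 0.10 | 2.066 | 0.039 | 1.054 | 80% | 83% |
| 0.20 | 2.191 | 0.028 | 1.118 | 82% | 87% |

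The formula assumes exact balance within strata. With 492/44 ≈ 11 women per stratum, incomplete blocks leave some imbalance, so this was simulated: 492 women, 44 strata, random blocks of 2 or 4 (assumed; the article gives no sizes), a separate effect per stratum in the adjusted model, 2,000 runs per setting.

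| R² | Null rejection, t-test | Null rejection, adjusted | Power, t-test | Power, adjusted |
|---|---|---|---|---|
| 0 | 0.047 | 0.048 | 79% | 78% |
| 0.10 | 0.036 | 0.048 | 81% | 84% |
| 0.20 | 0.026 | 0.046 | 81% | 86% |

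The simulation error is about √(0.05 × 0.95/2000) = 0.005 for the null rates and √(0.8 × 0.2/2000) = 0.009 for power. The simulation agrees with the formula. Where the strata explain nothing, adjusting for all 44 costs at most about one point of power.

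**Step 2: the entry value as covariate** (equal variances at entry and end, σ² = 1).

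- Final value alone: variance 1. Adjusted for entry value: 1 − ρ². For ρ = 0.5 and 0.7 this is 0.75 and 0.51, a cut of 25% and 49%, or 25–49%; stated as remaining variance, 75% down to 51%.
- In women, the same precision would need 246 × 0.75 = 184.5, rounded up to 185, or 246 × 0.51 = 125.5, rounded up to 126 per group.
- Change score: variance 2(1 − ρ). The ratio of adjusted to change-score variance is (1 − ρ²)/[2(1 − ρ)] = (1 + ρ)/2. For ρ = 0.5 and 0.7 this is 0.75 and 0.85, a cut of 25% and 15%. At ρ = 0.95 it is only 2.5%.

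**Step 3: which outcomes gain what.**

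| Outcome | Strata | Entry value |
|---|---|---|
| Insulin dose, if compared as a final value | yes | cut of 25–49% at ρ 0.5–0.7 |
| Weight gain, presumably a change score | yes | cut of 25–15% at ρ 0.5–0.7 |
| Neonatal fat mass, hospital stay | yes | none exists |

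The gains in the two columns overlap, since BMI group and entry weight carry shared information, and should not be added.

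**Step 4: gestational age at entry.** The window from 6 weeks 0 days to 22 weeks 6 days spans 16.86 weeks. If entry were uniform, an assumption, its SD would be 16.86/√12 = 4.87 weeks. It is known before allocation and can be a covariate for every outcome in the table. The documents give no basis for sizing that gain.

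**The case against.** The strongest reply is that nothing is broken. The t-test respects the randomised groups, errs on the conservative side and concerns secondary outcomes only. R² is not in the documents; at 5% the true alpha is 0.044, and at zero there is no loss. This stands, and it limits the point to efficiency and consistency.

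A second reply is that the sentence covers only outcomes taken at delivery, and the article does not say when insulin doses are compared. That also stands. If insulin dose falls outside the sentence, its analysis is left to a fuller document and is no fault here; the strata point remains for the others.

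A third is that the bootstrap option already provides flexibility. It deals with skewness, but a bootstrap that resamples women within each arm estimates the same unadjusted variance.

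A reader might infer more than the documents support:

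- That the plan ignores its repeated measurements. HbA1c has a mixed model; the remark can apply only to weight and insulin dose.
- That varying gestation at entry or delivery biases the comparison. Entry gestation precedes allocation and is balanced in expectation, so it adds noise. Comparing arms at delivery estimates a total effect by randomised group, in line with intention to treat. A comparison by gestational week targets a partly different quantity.
- That the large variance cut applies to all these outcomes. Step 3 shows that it does not.
- That the trial's 80% power would rise. That figure belongs to the binary primary outcome.

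**Conclusion.** The point holds as a matter of efficiency and consistency. The article fixes an unadjusted test for continuous secondary outcomes at delivery, while its randomisation and its binary analyses use site and BMI. The test is valid but conservative: true alpha about 0.044–0.028 and intervals about 3–12% too wide if the strata explain 5–20% of variance, and no loss if they explain none.

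Using the entry value would leave 75–51% of the variance of a final-value outcome at correlations of 0.5–0.7, with a smaller gain for weight gain and none for fat mass or hospital stay. The shares, correlations and equal variances are assumptions. There is no bias, no inflated type I error and no effect on the primary result. Because the article names the test, this concerns a stated choice and not an omission.

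**What to change.** Replace the t-test with a linear model for each continuous secondary outcome measured at delivery. Include treatment, site (fixed or random), BMI group and gestational age at randomisation, plus the entry value where one exists: entry weight for weight gain, entry insulin dose for insulin dose. Use bootstrap inference from that model if the outcome is skewed. State the time point at which insulin dose is compared.

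Optionally, analyse the repeated weights and insulin doses with the type of mixed model already planned for HbA1c, saying that this answers a partly different question from the comparison at delivery.

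The cost is analysis wording, settled before unmasking. No new data are needed: entry weight and insulin dose are in Table 1, and site, BMI group and gestational age are known from eligibility and randomisation.

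### An O'Brien–Fleming interim look at 0.003 is followed by a final test at the full two-sided 0.05, so the overall error slightly exceeds 0.05

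*Protocol article*

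**What the plan says.** Under Interim analysis and safety considerations, the protocol article states: "There is one planned interim analysis of the composite outcome after 50 % of subjects". This is put at n = 246. It invokes the O'Brien–Fleming procedure and adds that "the interim analysis will use a significance level of 0.003 for stopping the trial early".

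Under Final Analysis, the same composite is analysed by log-binomial regression: "The primary analysis will calculate the relative risk (and 95 % CI) of the composite neonatal outcome between the treated and control groups". The null hypothesis is a relative risk of 1, and the section closes with "All analyses will use a 2-tailed α of 0.05".

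The section Sample size and power calculation also uses a two-sided 0.05 with no allowance for the interim look: "A total of 246 women per treatment group gives 80 % power if the addition of metformin decreases the risk of the composite outcome" by 25 %. The article nowhere gives a final level below 0.05.

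**The concern.** O'Brien–Fleming is a set of boundaries, one for each look, chosen together so that the overall error is the stated level. The article takes up the first boundary and then gives a final level that belongs to a trial with no interim look.

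At stake is the threshold for the primary outcome. A final p-value between 0.049 and 0.050 would be declared significant under the Final Analysis text but not under the procedure named for the interim. The 95 % interval would likewise not correspond to the adjusted test. If the result fell there, the argument over which rule applied would take place after the data were known.

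**Working it through.** **Inputs**

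- Interim level 0.003, one interim look at 50 % of subjects (Interim analysis and safety considerations). The text does not give the side; 0.003 is taken as two-sided.
- Information fraction t = 246/492 = 0.5, with 492 = 2 × 246 (Sample size and power calculation).
- Final level 0.05, two-sided (Final Analysis).
- Event rates 50 % and 37.5 %, 246 per group (Sample size and power calculation); 1:1 allocation (Randomization).

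**1. The plan's own sample size**

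With the pooled-variance formula and no continuity correction, the mean rate is (0.50 + 0.375)/2 = 0.4375.

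- Standard deviation under the null: √(2 × 0.4375 × 0.5625) = 0.7016.
- Standard deviation under the alternative: √(0.25 + 0.375 × 0.625) = 0.6960.
- n = [(1.960 × 0.7016 + 0.8416 × 0.6960)/0.125]² = 246.06 per group.
- Power at 246: Φ[(√246 × 0.125 − 1.960 × 0.7016)/0.6960] = Φ(0.841) = 79.99 %.

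The stated 246 and 80 % are reproduced, at an unadjusted two-sided 0.05.

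**2. Overall type I error as written**

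Under the null, the interim and final statistics Z₁ and Z₂ are approximately bivariate normal with correlation √t = √0.5 = 0.707. The critical values are 2.968 (0.003) and 1.960 (0.05).

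Overall error = 1 − P(|Z₁| < 2.968 and |Z₂| < 1.960) = **0.05097**.

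A simulation of 20 million trials gave 0.0510. The simple sum, 0.003 + 0.05 = 0.053, is only an upper bound, because most trials that cross at the interim would also cross at the end: the probability of both is 0.0530 − 0.0510 = 0.0020.

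**3. Final level that restores 0.05**

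Solving 1 − P(|Z₁| < 2.968 and |Z₂| < c) = 0.05 gives c = 1.968, a two-sided final level of **0.0490**.

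**4. What 0.003 corresponds to**

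| Boundary at half information | Interim | Final |
|---|---|---|
| Lan–DeMets O'Brien–Fleming-type spending, 0.025 per side | 0.00305 | 0.0490 |
| Classical two-look O'Brien–Fleming | 0.0052 | 0.0480 |
| Article | 0.003 | 0.05 |

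The first row comes from 2[1 − Φ(2.2414/√0.5)] = 2[1 − Φ(3.170)] = 0.001525 per side, or 0.00305 in total. So 0.003 agrees with the spending-function version. Neither version has 0.05 as its final level.

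**5. Cost of the correction**

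- Power at 246 per group and final level 0.0490: Φ[(√246 × 0.125 − 1.968 × 0.7016)/0.6960] = Φ(0.833) = 79.75 %, a loss of 0.24 percentage points.
- Number for 80 % at 0.0490: 247.5, so 248 per group.

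**6. Sensitivity**

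- If the information fraction is 246/500 = 0.492, the overall error is 0.0510 and the final level is still 0.0490.
- If 0.003 permitted stopping in one direction only, as half of the two-sided region, the excess would be about 0.0005 instead of about 0.001.

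**The case against.** The best defence is that the closing sentence states the overall level and the sidedness of all tests. It ends a paragraph that also covers secondary outcomes, HbA1c and adjusted models, and it cannot literally govern every analysis, since the interim is run at 0.003. On that reading, naming O'Brien–Fleming with 0.003 at half information already implies about 0.049 at the end, and an article that condenses a fuller protocol may leave the exact critical value elsewhere. The consequence is also very small, and a conventional 95 % interval beside a slightly adjusted test is common practice.

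Part of this stands. The overall-level reading is possible, the effect is tiny, and the difference between 1.968 and 1.960 widens the interval by only about 0.4 %. Had the article said nothing about the final level, there would be no finding. But it does give a level, under the heading Final Analysis, beside an unadjusted 95 % interval for the primary relative risk, and that level does not match the procedure it names.

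**Conclusion.** The concern holds. As written, the plan has an overall two-sided type I error of 0.0510 rather than 0.05, and the final level consistent with 0.003 at half information is 0.0490. The practical effect is confined to final p-values between 0.049 and 0.050; the estimate and the planned sample size are unaffected.

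This rests on 0.003 being a two-sided nominal level, on the look falling at about half information, and on reading the closing sentence of Final Analysis as it stands. It should be corrected because it is the primary decision rule and the correction is almost free; the size of the effect does not support a stronger criticism.

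**What to change.** In Final Analysis, say that 0.05 is the overall two-sided level for the primary outcome, and that the primary composite is tested at the final analysis at two-sided 0.049 with a matching 95.1 % confidence interval.

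In Interim analysis and safety considerations, name the version of the boundary (Lan–DeMets O'Brien–Fleming-type spending fits 0.003), and say that the levels are recomputed from the spending function if the look does not fall at half information.

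The cost is two sentences and about 0.2 percentage points of power. No extra recruitment is needed: holding exactly 80 % would take 248 rather than 246 evaluable women per group, and the plan is to enrol 250 per group before loss to follow-up.

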### Data management

All data and statistical issues will be managed by the Centre for Maternal, Infant and Child Research and the trial statistician.

### Ethics committee approval

The study was approved by the Mount Sinai Hospital Ethics Review Board (Protocol No. NSP 104011) and by all the participating sites (see Additional file 1) at their local ethics boards.

